# Comparative effectiveness of guided internet-based stress management training versus established in-person group training in employees – study protocol for a pragmatic, randomized, non-inferiority trial

**DOI:** 10.1186/s12889-021-12229-y

**Published:** 2021-11-27

**Keywords:** Web-based intervention, Stress management, Occupational health, E-mental health, Randomized controlled trial, Non-inferiority trial

## Abstract

**Background:**

Occupational stress is a major public health challenge that requires a variety of evidence-based preventative approaches to increase their reach within the working population. Behavioral stress management interventions are considered an established approach for occupational stress prevention. Both in-person group-based stress management training (gSMT) and individual Internet-based training (iSMT) have been shown to be effective at reducing stress in employees. However, there remains a lack of evidence on the comparative efficacy of the newer digital format compared to well-established, in-person, group-based training. This study aims (1) to directly compare an evidence-based iSMT with an established gSMT on stress in employees, (2) to analyze the two conditions from a cost perspective, and (3) to explore moderators of the comparative efficacy.

**Methods:**

In a randomized, controlled, non-inferiority trial employees from the general working population will be allocated to iSMT or gSMT. The primary outcome will be perceived stress, assessed using the Perceived Stress Scale, three months after randomization. The non-inferiority margin for the primary outcome measure will be set at 2 points (Cohen’s d = 0.29). This trial will also compare the two interventions from a health economics perspective, and conduct explorative analyses to identify potential effect moderators.

**Discussion:**

To reach a larger proportion of the working population, well-established gSMT should be complemented with interventions that fit today’s society’s increasingly digital lifestyle. The current trial will provide evidence supporting the responsible implementation of Internet-based stress management training if the digital format proves to at least be non-inferior to established group-based training. Additional explorative moderator analyses may guide future practices to aid in matching select programs with select users.

**Trial registration:**

German Register of Clinical Studies (DRKS): DRKS00024892, date of registration: 2021-04-09.

Protocol version: 02, 16-10-2021.

**Supplementary Information:**

The online version contains supplementary material available at 10.1186/s12889-021-12229-y.

## Background

There is meta-analytic evidence documenting an association between work-related stress and an increased risk of developing severe disorders like depression [1], musculoskeletal conditions [2] and coronary artery disease [3–5]. Work-related stress also accounts for considerable societal costs, the majority due to productivity losses [6, 7].

In recent decades, numerous interventions have been developed and evaluated to protect workers from stress and its adverse health effects [8, 9]. Among the various measures developed to reduce stress, strong evidence exists suggesting beneficial effects from stress management training (SMT) [10–13]. Typically, SMT is offered as group stress management training (gSMT), mostly led by external trainers [10, 11]. At larger companies, specialized professional units for health and safety usually offer such mental health programs to the employees as in-house training programs. This requires organizational and financial resources, as well as the motivation of enough employees to participate in group training [14]. However, in the United States, for example, about half of all employees currently work at a small or medium-sized company [15], and similar figures exist for the European Union [16]. Furthermore, employers may not always be aware of the business benefits of employee health interventions [17]. Additionally, some practical issues specific to small businesses may hamper the provision of gSMT. Examples of this are the non-availability of service providers in rural areas [14] and inadequate numbers of employees to justify in-house group training at small businesses. One alternative is joint group training involving employees from multiple companies. Potential disadvantages of this are that such training might require extra travel-time to reach the venue and a loss in autonomy due to externally-determined time schedules.

To overcome some of the barriers of in-person group stress management training, Internet-based interventions have been advocated as an alternative [18]. They fit with an increasingly digital lifestyle and employees can use Internet-based stress management training (iSMT) at any time and place, at their own pace, and without the time and costs required for travel. Moreover, anonymous participation is possible, if participants prefer to not disclose struggling with stress to their colleagues and/or employer. Studies have shown that iSMT can be effective in different employee groups with, on average, moderate-to-large effects, in terms of reducing stress [19, 20]. In addition, meta-analyses have revealed small to moderate effects on the symptoms of depression and anxiety [20, 21], large effects on insomnia [20] and even effects on work productivity [22]. ISMT appears to work, either with or without additional human support (i.e., guided by written feedback on training assignments), but guided interventions generate larger mean effects than unguided programs [19]. Moreover, initial studies have shown that iSMT can be cost-effective for both employers [23] and society [24], relative to non-active control conditions.

However, the majority of previously published studies compared interventions to non-active control conditions [19]. These results are helpful for deciding whether iSMT is effective in principle. For policy and decision makers, however, it is critical to have robust evidence indicating whether iSMT is as effective at reducing stress as existing group and in-person SMT programs. Currently, there is only indirect evidence that iSMT might be an adequate alternative to established in-person SMT. For example, the effect size of in-person SMT programs on stress was Cohen’s d = .73 in a meta-analysis published by Richardson and Rothstein (2008). Meanwhile, in a recent meta-analysis on Internet-based interventions for employees, Hedges’ effect size g was .76 for guided interventions [20]. This said, there was significant heterogeneity in the two meta-analyses. To this end, we consider it particularly important to compare the effectiveness of these two different types of intervention directly in the same study.

Few randomized controlled trials have compared the effects of stress management training in offered in different forms (i.e., gSMT versus Internet- or computer-based SMT) [25, 26]. Findings to date have revealed no significant difference between these interventions, with regard to stress reduction [25, 26]. Although these studies suggest that employees benefit equally from iSMT and gSMT, such a conclusion must be considered premature. Statements about equivalence or non-inferiority require adequate sample calculations and a pre-defined margin of equivalence or non-inferiority [27]. Given non-inferiority regarding mental health benefits, it is also important to allocate limited financial resources as efficiently as possible. Therefore, trial-based economic evaluations are recommended, since comparing the costs and consequences of gSMT and iSMT can provide valuable information for policymakers [28].

In the recent years, different iSMT programs, like “GET.ON Stress”, have been implemented in routine care. This program has already been evaluated in a series of randomized controlled trials in the general working population with elevated stress, demonstrating significant effects, in terms of reducing stress and depressive symptoms, relative to be being on a waiting list [29–31]. Moreover, economic evaluation of the intervention indicates that it is likely to be of good value for the money in occupational healthcare [23]. In this trial, the iSMT “GET.ON Stress” will be compared to the established in-person gSMT intervention — “Gelassen und sicher im Stress “[Calm and safe under stress] [32, 33] — which may be the most often used stress management training program in German-speaking countries and has been demonstrated in a randomized controlled trial to be effective at reducing stress, as well [33, 34].

As for any complex intervention, beyond comparative efficacy and cost-effectiveness, it is important to obtain insights into moderators of the SMT under study [35]. While assessing the non-inferiority of iSMT, in terms of reducing stress, it would also be valuable to explore if there are indicators that identify who benefits most from which SMT format. Research on moderators of either format, however, is scarce. For group stress management training, different intervention- and person-related moderators of efficacy have already been studied (e.g., intervention length, an intervention’s number of components, industry sector) [10] without generating clear conclusions for implementation in occupational settings. On average, iSMT yields greater effects when complemented with guidance through personal contact, contrary to pure self-help interventions [19, 20] and when it takes no more than nine weeks to finish the intervention [19]. Identifying moderators for each of these formats would provide novel information for intervention developers and decision makers, both in public and occupational health, especially if non-inferiority is established. For example, one study evaluating how well different health service formats were accepted by respondents of the general population revealed that people found face-to-face counselling and therapies more useful than Internet-based counselling, and that participants reported greater intentions to use face-to-face services to address emotional problems [36]. Similarly, respondents to another survey preferred traditional face-to-face stress management over Internet-based stress management [37]. To our knowledge, no study to date has empirically investigated the characteristics of the different training formats as potential moderators of these interventions’ efficacy.

In keeping with the above issues, the primary objective of this pragmatic trial is (1) to test the hypothesis that the iSMT intervention “GET.ON Stress” [29] is non-inferior to the gSMT intervention “Gelassen und sicher im Stress – calm and safe under stress” [32, 33] in employees, in terms of reducing perceived stress. Further aims are (2) to compare the two conditions from a cost perspective, and (3) to explore moderators of this comparative efficacy.

## Methods

### Study design

The declaration of Helsinki for Ethical Principles for Medical Research Involving Human states that “The benefits, risks, burdens and effectiveness of a new intervention must be tested against those of the best proven intervention(s)” [38]. Accordingly, we will test the non-inferiority and cost-effectiveness of the relatively new iSMT intervention “GET.ON Stress” [29] against the best proven and probably most adopted intervention for stress management in Germany speaking countries, that is the gSMT intervention “Gelassen und sicher im Stress – calm and safe under stress” [32, 33]. In a randomized controlled trial, one group of participants will receive access to iSMT, whereas another group will participate in gSMT.”

Outcome assessments will take place at baseline (T1), and both three months (T3) and six months (T4) after allocation to the study conditions. To mimic real-life occupational practice, participants in iSMT will be granted access to the intervention immediately after randomization, whereas participants in gSMT will have to wait until a sufficiently large number of participants has been recruited and randomized into this condition to fill group sessions. For this reason, participants in each condition will also need to attend in a short extra assessment (T2) right before their first training session.

The primary outcome will be the level of perceived stress at T3. There will be no restrictions to the use of other care as usual (CAU). This study protocol describes the design of the pragmatic trial based on Standard Protocol Items: Recommendations for Interventional Trials (SPIRIT) guidelines [39]. The study also will be conducted in accordance with the Consolidated Standards of Reporting Non-inferiority Trials (CONSORT) [27].

### Participants

The target group will consist of workers from small- and medium-sized enterprises. For pragmatic reasons, the study will take place in the Rhine-Ruhr metropolitan region in Germany, which has a population of approximately 10 million people. Participants must a) be employed, b) have access to the Internet to complete online training sessions weekly, c) be able to visit gSMT sessions in their local area, d) give their informed consent to participate, and e) complete the baseline assessment (T1). Referring to national guidelines for prevention, we keep the exclusion criteria at a minimum. Applicants a) who are participating in another stress management training at the time of study registration will be excluded. To ensure participants’ safety, those b) with an elevated risk of suicide, indicated as a score > 1 on item 9 of the Beck Depression Inventory [40], will be also excluded and receive an email containing information about how to obtain adequate help and listing the telephone numbers of relevant services.

### Recruitment and procedures

Recruitment will occur in the winter through summer of 2022, employing two major strategies. To attract interested organizations, we will use different media channels to motivate owners of small- and medium-sized companies (staff headcount < 250) in the target region to offer the intervention to their workforce. To attract individuals, health insurance companies will advertise the study via announcements in print membership magazines and media channels (e.g., Facebook, Twitter). Registration into the study will take place at an individual level, so employees need not self-disclose to their employer that they want to participate. An open-access website will provide information on study conditions. Applicants will sign up by providing an email address and name or pseudonym on the website. Applicants who fulfill all inclusion criteria assessed by an online screening questionnaire, return their informed consent, and complete the baseline assessment (T1) will receive a phone call by a research assistant to inform them about further requirements for inclusion (e.g., time scheduling for each of the interventions) and to answer the applicants’ questions. Thereafter, each applicant will be randomly allocated to one of the study conditions (Fig. 1), with randomization stratified by whether or not employees work in companies concurrently conducting organizational mental health programs. Allocation concealment will be ensured by an independent researcher not otherwise involved in this study, who will randomize study participants with a separate randomization sequence for each strata (concurrent organizational health program = yes/no). We will use a restricted randomization procedure using varying block sizes of 4 to 6 generated by the software RandList (randomization.eu). This researcher will send randomization results to the study administration responsible for subject allocation. For practical reasons, blinding of participants will not be possible.

After they are informed about the outcome of randomization, participants offered iSMT will receive immediate access to the program. Participants allocated to gSMT will receive information about the times and locations of group sessions; they then will need to select in which workshop they want to participate. Just before their first training session, all participants will need to complete a short pre-intervention assessment (T2). Participants will receive up to three automated e-mail reminders if they did not attend the assessments. All assessment and Internet-based training data will be collected using a secure assessment and training system (AES, 256-bit encrypted). Both the web-based assessment system and training platform are physically located on servers belonging to Leuphana University of Lueneburg. The principal investigator DL and the first author LB will have full access to the final dataset. Two researchers will assure data integrity, independently.

**Fig. 1 Fig1:**
[figure not shown]
Study Flow

### Intervention conditions

#### Internet-based stress management training

The iSMT program “GET.ON Stress” [29, 41] was designed to enhance two strategies of stress coping: problem solving [42] and emotion regulation [43] (Table 1). The intervention consists of seven modules that participants should work on following a weekly schedule. Each module consists of general information; interactive exercises; prototype training participants – so called *personas* – who represent different stressed employee groups; quizzes; audio and video files; and downloadable work sheets. In addition, at the end of sessions 2 to 6, users can choose to attain extra information and perform short exercises about the following common stress-related topics: time management, rumination and worrying, psychological detachment from work, sleep hygiene, sleeping habit rhythm and regularity, nutrition and exercise, organization of breaks during work, and social support [29, 41]. For this trial, we adapted GET.ON Stress to employees working at small- to medium-size enterprises, the adaptation pertaining to the personas within the online program who guide participants through the program. Personas are a well-established element of user-centered design in software engineering [44] that has been also used to tailor Internet-based interventions to specific target groups [45, 46]. Within GET.ON Stress, the personas fulfill several functions, following the Efficiency Model of Support [47]. The integration of personas aims to increase user engagement in the iSMT program, providing knowledge about how to complete the exercises within the program and helping users to transfer what they learn from the exercises into their daily lives; for instance, by giving examples of how employees working under similar circumstances apply a given problem-solving strategy in their daily life. In addition to program content, participants will receive written feedback from an e-coach on their exercises after each of training module, the feedback provided in accordance with the training manual. E-coaches will be psychotherapists or master’s degree-level psychologists. Based upon our experiences from previous studies, we anticipate that the e-coaches will spend roughly 30 min per feedback. To improve participants’ adherence with the intervention, the e-coaches will send reminders to participants any time they fail to complete a training module within seven days. All communication between the participant and the e-coach will take place in a secured, web-based, open-source platform, located at the Leuphana University of Lueneburg.

**Table 1 Tab1:** Content of the Internet-based intervention

Session^a^	Intervention content
1	Psychoeducation on stress and coping competencies Enhancement of pleasant activities
2	Problem-solving I – identifying and differentiating solvable and unsolvable problems; developing an initial problem-solving plan Information and exercises on selected topics, which users can self-select^b^
3	Problem solving II – self-evaluating the problem-solving plan; adapting or developing a new problem-solving plan Information and exercises on selected topics, which users can self-select^b^
4	Emotion regulation I – progressive muscle relaxation Information and exercises on self-selected topics^b^
5	Emotion regulation II – acceptance and tolerance of (negative) emotions Information and exercises on self-selected topics^b^
6	Emotion regulation III – effective self-support in times of stress Information and exercises on self-selected topics^b^
7	Developing a stress-coping plan for the future

Note: ^a^ each session will last approximately 45 to 90 min; ^b^ optional exercises will cover the topics of time management, rumination and worrying, psychological detachment from work, sleep hygiene, the rhythm and regularity of sleeping habits, nutrition and exercise, organization of breaks during work, and social support

3	6	Enhancing pleasant activities II Cognitive restructuring of dysfunctional attitudes Problem-solving II - self-evaluating the problem-solving plan; adapting or developing a new problem-solving plan
	7	Developing a personal health promoting project for the future

Note: ^a^ Each day of training will last three hours and be comprised of different thematic training sessions. For each group, all training days will take place within seven weeks; ^b^ participants will be instructed to practice the relaxation technique regularly on their own between the training days. On training days 2 and 3, they can share their experience with the technique and ask for any needed assistance

### Outcome measures

#### Primary outcome

The primary outcome will be the level of self-rated stress (Table 3), measured using the Perceived Stress Scale (PSS-10) [49], a validated measure of stress that has been used extensively during evaluations of both in-person and Internet-based stress-management interventions. The PSS-10 assesses the extent to which participants experience their lives as stressful (e.g., as overstraining, unmanageable, and/or unforeseeable over the past month). It consists of ten items, each having the following 5-point Likert scale response options of 0 = never; 1 = almost never; 2 = sometimes; 3 = fairly often; and 4 = very often (summation score range 0–40). In this trial, respondents will answer items referring only to the past week. The German version of the scale has been validated in the general population [50]. An online version of the German scale has also been validated in samples of German employees, exhibiting good reliability with McDonald’s omega (ω) = .89 and good measurement invariance [51].

**Table 3 Tab3:** Outcome measures and assessment points

Outcome measures	T0	T1	T2	T3	T4
Perceived Stress Scale (PSS)	✓	✓	✓	✓	✓
Center for Epidemiological Studies on Depression Scale (CES-D)	-	✓	-	✓	-
Brief Resilience Scale (BRS)	-	✓	-	✓	-
Perceived Occupational Stress (POS)	-	✓	-	✓	-
Technology Readiness (TRI 2.0)	-	✓	-	-	-
Patient Questionnaire on Therapy Expectation and Evaluation (PATHEV) – adapted for stress management training	-	✓	-	-	-
Effort-Reward-Imbalance Questionnaire (ERI)	-	✓	-	✓	-
Job Crafting Scale (JCS) - adapted	-	✓	-	✓	-
Treatment Inventory of Costs in Psychiatric Patients (TIC-P), subscale for productivity loss	-	✓	-	-	✓
Health and Labor Questionnaire (HLQ)	-	✓	-	-	✓
Assessment of Quality of Life (AQoL-6D)	-	✓	-	-	✓
Client Satisfaction Questionnaire (CSQ/CSQ-I)	-	-	-	✓	-
Preferences for online and group stress management - self-developed	-	✓	-	✓	-
Adherence to the intervention - self-developed	-	-	-	✓	-
Beck Depression Inventory (BDI), suicide ideation item	✓	-	-	-	-
Socio-economic variables (staff headcount, including income from paid employment, history of health service use, current health-related change programs in the organization, preference for Internet-based vs. in-person group training for stress reduction)	✓	-	-	-	-

Note: T0 = Screening for eligibility; T1 = Baseline Assessment; T2 = Pre-Intervention Assessment prior to intervention beginning; T3 = Post-Intervention-Assessment, 3 months after group allocation; T4 = Post-Intervention-Assessment, 6 months after group allocation

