#### Cost-effectiveness measures

To collect health service utilization and productivity losses, we will use the Treatment Inventory of Costs in Psychiatric Patients (TIC-P) [60], adapted to the German context. This questionnaire includes different single questions to estimate the impact of presenteeism on productivity losses. To estimate productivity loss due to impaired performance directly, we adapted an item extracted from the Health and Labor Questionnaire (HLQ) [61]: “If you now have to catch up on work that you have not done in the last 4 weeks due to your health problems, how many hours would you have to work?”. For cost-utility analyses, we will calculate quality-adjusted life years (QUALYs), based on the Assessment of Quality of Life (AQoL-6D) [62].

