### Economic evaluations

We will perform economic evaluations from different perspectives. From an employer’s perspective, we will conduct cost-benefit analysis (CBA), considering opportunity costs due to the time required for employees to partake of the intervention and changes in productivity loss due to reduced absenteeism and presenteeism. Since health insurance companies in several countries are legally obligated to fund preventative actions, we will conduct a separate CBA from an insurer’s perspective, including intervention costs, reflected as the common market prices for the interventions. In addition, we will conduct cost-effectiveness analysis (CEA). For the CEA, we will calculate intervention costs and costs due to productivity loss and effects of the interventions, in terms of the number of reliable improvements in perceived stress at T4. The costs and effects of both interventions will then be combined in an incremental cost-effectiveness ratio [28]. A non-parametric boot-strapping method with 95% confidence intervals will be used to account for the uncertainty of differences between the two intervention groups. Finally, we will determine the probability that the intervention is cost effective for different values of willingness-to-pay per effect unit.

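### Text and Table 3 disagree on whether the TIC-P records health service use; if Table 3 is followed, the insurer cost-benefit analysis is only a price comparison

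*Protocol article*

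**What the plan says.** Three places in the protocol article bear on this point.

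- **Cost-effectiveness measures:** "To collect health service utilization and productivity losses, we will use the Treatment Inventory of Costs in Psychiatric Patients (TIC-P"), in a version adapted to Germany. The section adds one HLQ item on catching up on "work that you have not done in the last 4 weeks due to your health problems". It gives no recall period for the TIC-P.
- **Table 3 (under Primary outcome):** the row reads "Treatment Inventory of Costs in Psychiatric Patients (TIC-P), subscale for productivity loss" and is ticked at T1 and T4. The HLQ row has the same two ticks. Health service use appears only as a history among the socio-economic variables, ticked at T0. The table note gives "T4 = Post-Intervention-Assessment, 6 months after group allocation".
- **Economic evaluations:** the employer cost-benefit analysis uses opportunity costs of training time and changes in productivity loss. The cost-effectiveness analysis uses intervention costs, productivity-loss costs and reliable improvements at T4. For the insurer there is a "separate CBA from an insurer’s perspective, including intervention costs, reflected as the common market prices for the interventions". No benefit item is named for it.

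**The concern.** A cost-benefit analysis sets a cost against a benefit. For a health insurer the natural benefit is health-service cost avoided, and it can be estimated here only if service use is recorded in both arms after allocation. The text says it will be; the assessment schedule says it will not. Questionnaires are normally programmed from the schedule, so the omission could easily be carried into the data, and service use that is not asked about at the time cannot be reliably reconstructed later. Comparing the two formats from a cost perspective is the trial's second stated aim, and the Discussion presents the economic comparison as a first of its kind.

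A second, smaller question is how much of the six months the productivity instruments observe. Neither is given at T3, and the arms start training at different times by design: iSMT at once, gSMT after a wait.

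**Working it through.** The protocol states no figure for this point, so there is none to reproduce. The check has two parts.

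**1. Which planned analysis needs which data, and does Table 3 supply them after randomisation?**

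| Analysis (Economic evaluations) | Inputs named | Scheduled after allocation in Table 3? |
|---|---|---|
| Employer cost-benefit | time cost of training; productivity loss | Productivity: yes, TIC-P subscale and HLQ item at T4 |
| Cost-effectiveness | intervention cost; productivity loss; reliable improvement on the PSS at T4 | Yes, all survey inputs at T4 |
| Insurer cost-benefit | market price of the courses; no benefit named | Health service use: no, only a history at T0 |

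For the insurer:

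net benefit of iSMT over gSMT = (health-service cost in gSMT − health-service cost in iSMT) − (price of iSMT − price of gSMT)

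If Table 3 governs, the first bracket has no data and only the price bracket is left. If the Cost-effectiveness measures text governs, the first bracket can be estimated. The article does not say which governs.

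**2. Share of follow-up seen by a single measurement at T4**

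Inputs: T4 is 6 months after allocation, taken as 26 weeks (Table 3 note). The HLQ recall is 4 weeks (Cost-effectiveness measures). The TIC-P recall is not stated, so a range is assumed.

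coverage = recall window ÷ 26 weeks

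| Instrument and recall | Coverage from T4 | Weeks after allocation not covered |
|---|---|---|
| HLQ item, 4 weeks (stated) | 4/26 = 15% | 26 − 4 = 22 |
| TIC-P, 4 weeks (assumed) | 4/26 = 15% | 22 |
| TIC-P, 3 months = 13 weeks (assumed) | 13/26 = 50% | 13 |
| TIC-P, 6 months = 26 weeks (assumed) | 26/26 = 100% | 0 |

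The T1 measurement looks back from before allocation, so it adds a baseline level but no coverage of follow-up.

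Effect of adding the items at T3 (3 months): with a 3-month recall, T3 and T4 together cover 2 × 13 = 26 weeks, the whole period. With a 4-week recall they cover 2 × 4 = 8 weeks, 8/26 = 31%, and supply a mid-point level. With a 6-month recall the TIC-P gains nothing.

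**The case against.** The strongest reply is that this is an inconsistency, not a proven omission. A reader might infer from Table 3 that the insurer analysis has no benefit side at all. The documents do not support that: the text states that the TIC-P will collect health service use, and the insurer sentence introduces intervention costs as something included, not as a closed list. The benefit input is undetermined. This part of the objection stands, and the point is worded accordingly.

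A reader might also infer that productivity loss goes unmeasured for the first five months or so. That is shown only for the HLQ item, whose 4-week window is printed. With a 6-month recall the TIC-P would leave no gap. Nor do the documents say that the remaining weeks are extrapolated from T4; both instruments are also given at T1, and how costs are built up between assessments is something an article may leave to the full plan. This stands too.

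It can further be said that the delayed gSMT start is disclosed under Study limitations as a real-life feature, that the cost-effectiveness endpoint is itself at T4, and that no figure is given for how productivity differs between arms over time. A T3 cost assessment is therefore not the correction of an error in itself. That is fair, and it makes the T3 addition conditional.

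What the reply does not remove is that two printed statements about the same instrument disagree. This is not detail left to a fuller document.

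**Conclusion.** The point holds as a contradiction between the Cost-effectiveness measures text and Table 3 on the content of the TIC-P. Its consequence is confined to the insurer cost-benefit analysis: if Table 3 is followed, there is no measured health-care saving to set against price, and the result is the price difference between the two courses. The employer analysis and the cost-effectiveness analysis draw on inputs that Table 3 does schedule, and the primary non-inferiority analysis is untouched. It should be settled before the questionnaires are fixed, because one part of the second aim depends on it.

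On coverage, the firm statement is limited to the HLQ item: about 15% of the six months, taking 6 months as 26 weeks. For the TIC-P the figure lies anywhere from about 15% to 100%, depending on a recall period that the article does not give.

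**What to change.** 1. Reconcile Table 3 with Cost-effectiveness measures: schedule the TIC-P health-service-use section at T1 and T4 in both arms, and amend the Table 3 row to say so.
2. In Economic evaluations, name avoided health-service cost as the benefit in the insurer cost-benefit analysis. If service use will not be collected, call that analysis a price comparison and correct the Cost-effectiveness measures text.
3. State the TIC-P recall period. Only if it is too short to cover the six months from T4, add the productivity items to the T3 online questionnaire that participants already complete. With a 4-week recall this still leaves gaps, so the assumption used between assessments should then be stated.

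The cost is a few more items in existing online questionnaires and slight respondent burden, with no extra visit or staff. The relabelling option costs only wording, but gives up the insurer's benefit question.
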